### Sample size

It has been reported that the incidence of CVD events is about 6%.^31^ According to Liu *et al*,^32^ among 24 IgG glycan peaks (GPs), GP6 is significantly different between people with and without ischaemic stroke (5.00 (4.26, 5.85) vs 4.48 (3.93, 4.35), p=0.028) and therefore can be used to roughly estimate the sample size. Converting median and quartile to mean and SD is necessary for the sample size.^33–35^ Taking the incidence of CVD events and this conversion into consideration, 2267 participants will be needed, based on an α of 0.05 on a two-sided test and 90% power, to obtain a statistical difference. An additional one-fifth is required for the total sample size when considering cases of lost to follow-up and refusal to visit. Finally, a total of 2720 participants are required for the study. The sample size was calculated using PASS software (V.11; NCSS, America).

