### Statistical and analytical plans

Categorical variables will be expressed by frequency (percentage) and univariate analysis will be performed using the χ^2^ test. Data of normal distribution are shown as mean±SD. The t-test and analysis of variance are used for comparison of two groups and multiple groups, respectively. Non-normally distributed data are represented by median (P25, P75). Univariate analysis is performed by non-parametric testing. Interpolation is carried out according to the type of data loss. If the lost data are of numerical type, the average value is used to fill it. However, if the lost data are non-numerical, the value with the highest occurrence frequency in this index is filled in. Logistic regression will be applied to analyse the association between IgG N-glycosylation characteristics and CVD events. Subsequently, a glycan risk score will be created to evaluate the associative effects of all glycan traits screened. A p value <0.05 indicates statistical significance. SPSS software (V.26.0) will be used for statistical analysis.

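### A flat p<0.05 across all glycan traits, in a biomarker-screening study sized for one peak, inflates false positives and can make the glycan risk score look predictive when it is not

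*Protocol article*

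**What the plan says.** All the statements are in the protocol article.

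- **Threshold.** Statistical and analytical plans gives one rule for all testing: "A p value <0.05 indicates statistical significance". It is not limited to a primary comparison.
- **Analysis and score.** The same section relates IgG glycan characteristics (plural) to CVD events by logistic regression. After that, "a glycan risk score will be created to evaluate the associative effects of all glycan traits screened".
- **Aim.** The abstract's methods paragraph names the screening of potential CVD biomarkers as a purpose of the study.
- **Sizing.** Sample size rests on one peak from a cited study: "among 24 IgG glycan peaks (GPs), GP6 is significantly different between people with and without ischaemic stroke". The calculation is "based on an α of 0.05 on a two-sided test and 90% power", and from it "2267 participants will be needed", with an expected event incidence of about 6%.
- **Cohort.** Design and setting and the Discussion describe one single-centre cohort. The Discussion leaves a multicentre cohort to further work.

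**The concern.** A threshold of 0.05 limits the false-positive rate to 5% for one test. Here it is applied to a panel of glycan traits with the purpose of picking out those that look associated with events. The sample size makes no allowance for that, because it provides for one peak at 0.05.

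The score adds a second problem. If traits are chosen because they separated cases from non-cases in this cohort, a score built from them will also separate cases from non-cases in this cohort, whether or not any trait carries information. The Introduction hypothesises that the glycan profile is an independent prognostic indicator, and the Discussion envisages a marker that predicts better than GlycA. Claims of that kind are directly exposed to this optimism.

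**Working it through.** **Inputs from the article:** threshold 0.05; 24 peaks (in the cited study); evaluable sample 2267; incidence about 6%; GP6 median (quartiles) "5.00 (4.26, 5.85) vs 4.48 (3.93, 4.35), p=0.028".

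**Assumptions of this review:** 24 tests; a common correlation of 0, 0.3, 0.5 or 0.7 between traits (the article gives none); no true association.

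**1. The plan's own figure.** Take mean = (q1 + median + q3)/3, SD = (q3 − q1)/1.35, and n per group = (1.960 + 1.282)² × (s₁² + s₀²)/d².

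- As printed, the second group's upper quartile (4.35) lies below its median (4.48). The formula then gives d = 0.783 and n = 25.4. That is 26 cases, and 26/0.06 = 433 participants (450 with the rank-test factor π/3). Neither is 2267.
- If 4.35 is assumed to be a misprint for 5.35: means 5.037 and 4.587, d = 0.450, SDs 1.178 and 1.052, n = 129.4. Then 129.4 × π/3 = 135.5, rounded up to 136 cases, and 136/0.06 = 2266.7, which is 2267. Also 2267 × 1.2 = 2720.4, which matches the stated 2720.

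On this reconstruction the figure comes from one comparison at 0.05.

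**2. False positives across the panel.**

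- Expected number: 24 × 0.05 = 1.2.
- Chance of at least one, independent tests: 1 − 0.95²⁴ = 0.708.
- Chance of at least one, equicorrelated tests (simulated):

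| Assumed correlation | P(at least one) |
|---|---|
| 0 | 71% |
| 0.3 | 60% |
| 0.5 | 46% |
| 0.7 | 31% |

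At a correlation of 0.7 the rate is still about six times 5%. For independent tests, a 95% chance needs ln 0.05/ln 0.95 = 58.4, so 59 tests.

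**3. The score under pure noise.** Events: 0.06 × 2267 = 136; non-events: 2267 − 136 = 2131. Simulate 24 null traits, keep those with p<0.05, form a weighted sum, and assess it in the same data. Over correlations of 0 to 0.7:

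- a score is formed in about 72% of runs at correlation 0, falling to about 30% at 0.7;
- its mean apparent AUC, when formed, is 0.57 falling to 0.56 (truth 0.50);
- its parametric p value is below 0.05 in 100% of the runs that form a score, and its rank-test p value in about 87% to 90%.

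**4. Cost of adjusting.** Bonferroni uses 0.05/24 = 0.00208, with a familywise error of 1 − (1 − 0.00208)²⁴ = 4.9% under independence. Use the GP6 effect with the assumed quartile 5.35: 0.450/√((1.178² + 1.052²)/2) = 0.40 SD. With 136 events against 2131 non-events and separate group variances, power is 98.9% at 0.05 and 87.9% at 0.05/24 with the rank-test factor (89.8% at 0.05/24 without it).

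**The case against.** **The threshold sentence is boilerplate, and the article is condensed.** A fuller plan might define the trait family, adjust for multiplicity and validate the score. This has force for validation: silence on it is not a fault in an article. It has less force for the threshold, which is stated without qualification for a study that screens. A fuller plan that adjusted would have to override it.

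**Several premises are inferred.** This stands. The number 24 describes the cited study. The article does not say that p<0.05 decides entry to the score, and the wording about the traits screened could mean every trait examined. Nor does it say how the score will be judged. The score result above is therefore conditional.

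**Observational work tolerates unadjusted screening.** No treatment decision hangs on these p values, and a follow-up study could weed out false leads. That lowers the severity. It does not remove the problem, because the stated hypothesis is about independent prognosis, which is more than generating leads.

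**A reader might infer that adjustment would wreck the power.** A fall from 90% to 57% appears if 136 cases are compared with only 136 non-cases, or if the effect is back-solved as the smallest one detectable with 90% power (0.287 SD). Neither describes the planned comparison. With the cohort's actual split and the GP6 effect as reconstructed, power at 0.05/24 stays near 88% to 90%.

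**Conclusion.** The point holds as a should-fix. The stated rule does not control error across the glycan traits, and nothing in the sample size allows for multiple tests. With about 24 tests and no true association, 1.2 false positives are expected. The chance of at least one is at most about 71%, and about 31% to 60% at assumed correlations of 0.7 to 0.3. If traits enter at p<0.05 and the score is assessed in the same participants, noise alone yields an apparent AUC of about 0.56 to 0.57, and the score's parametric p value carries no information.

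A reader might infer that false positives are near certain, or that an inflated score is guaranteed. The documents do not support that. Near certainty needs a larger family, such as all four serum time points tested separately (96 tests: 99% if independent, 94% down to 49% at correlations of 0.3 to 0.7), and the article does not define one. The figures also describe the global null; if some traits are truly associated, some findings will be real.

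**What to change.** In Statistical and analytical plans:

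1. State which glycan traits are tested, and at which time points. Replace the flat threshold for them with Benjamini-Hochberg control of the false discovery rate at 5% across all traits within each outcome. Bonferroni is an acceptable alternative.
2. State how traits enter the score and how they are weighted. Report the score's association and AUC after bootstrap optimism correction, repeating selection and weighting in every resample.

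Naming GP6 as the sole confirmatory test, or building the score by penalised regression, would also be reasonable, but both are optional. GP6 was used only for a rough sizing, and its evidence concerns ischaemic stroke, not the full composite.

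**Cost.** Wording and some computing; the bootstrap may need software beyond standard SPSS menus. There will be fewer nominal hits and less power for small effects. Recruitment, sampling and follow-up do not change.

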### Monitoring

This study will be conducted critically according to the approved proposal. The data and safety monitoring committee (DMC) of our hospital will undertake the responsibility of data review and interpretation, which is beneficial to the security and privacy of the participants and to the validity and integrity of the data. Six researchers, independent of the sponsor and conflict of interest, make up the DMC, which will evaluate the data after a quarter, a half and three-quarters of the participants voluntarily enrol in this study. The six researchers will be involved in the entire research progress.

### Auditing

Based on state regulations, the audit work will be conducted during the entire study process to trace the changes and guarantee the quality of research data. Representatives from the ethics committee will shoulder the obligation to inform the related parties of all proposal revisions.

### Harms

This non-intervention study is remarkably safe. Participants will get no exposure to any drug-related or surgery-related therapies.

### Amendment

Any modifications to the proposal will be submitted to the Clinical Ethics Committee and DMC for consent.

## Ethics and dissemination

### Ethics approval

The study protocol was approved by the Clinical Ethics Committee of the First Affiliated Hospital of SUMC on 13 July 2021 (number: B-2021-127).

### Informed consent

Before enrolment, the investigator will introduce the main purpose and content of the study to the participants. In addition, participants will be informed of the possible risks and benefits of the research to ensure that their participation is completely voluntary. After participants have signed the informed consent, all study-related data, including personal information, will be kept confidential. This study will be carried out in accordance with the principles of the Declaration of Helsinki.

### Dissemination

All data and findings of this study will be disseminated at scientific conferences or submitted for publication in peer-reviewed journals.

## Discussion

AS can lead to acute myocardial infarction, cerebral infarction and other serious consequences, which seriously affect quality of life and bring a huge economic burden to patients and society. It has been reported that at the beginning of 2010 the total hospitalisation cost of patients with CVD was over ¥40 billion, which contributes to more than 1.60% of the national health expenditure.^37^ ASCVD has become a major public health problem worldwide, making the prevention and treatment of CVD urgent.

A large amount of evidence shows that the pathogenesis of AS is mainly related to the adaptive immune-inflammatory response. AS contains IgG antibodies against LDL, oxidised LDL and apolipoprotein B (ApoB).^38^ Some studies suggest that IgG antibody titre is positively correlated with AS, whether in mice or humans,^39^ and that anti-ApoB IgG antibody can aggravate AS.^40^ In vitro experiments demonstrate that IgG and very low-density lipoprotein are responsible for forming arterial lesions.^41^ As an immunoinflammatory biomarker, IgG glycosylation is effective in differentiating patients with dyslipidaemia from the healthy, displaying an area under the curve of approximately 0.7 in a cross-sectional study of Chinese Han.^27^ Removal of glycans contributes to the disappearance of the anti-inflammatory properties of IgG,^42^ while the enrichment of sialic acid is responsible for a 10-fold increase in the anti-inflammatory properties of IgG.^43^ Therefore, control of the adaptive immune response through immune regulatory strategies or vaccination is a potential therapeutic direction for AS.

Glycoprotein acetylation (GlycA), a more reliable compound biological marker of systemic inflammation, has potential value in predicting CVD outcomes and reflecting inflammation.^29 44–47^ However, GlycA is a glycan signal of a single measure based on nuclear magnetic resonance. Therefore, the association between IgG N-glycosylation with richer glycoprotein traits and CVD composite events will be assessed in this study. If the results of this study show a significant correlation between IgG glycosylated traits and actual clinical CVD composite events, it will provide further evidence on the role of glycosylation modification and immune-inflammatory response in AS, as well as a potential biomarker better than GlycA in predicting CVD events in the clinic. In addition, clarifying the correlation between IgG and AS and revealing the mechanism of atherogenesis are essential to providing new directions for treatment and prevention of CVD. Our study will provide important scientific significance and socioeconomic value for improving the quality of life and decreasing the mortality rate and the socioeconomic burden of patients with CVD.

However, some limitations to this study exist. First, the participants are recruited at a single centre and represent only one ethnic group, Han Chinese, in the Chaoshan area of Guangdong Province and thus lack ethnic diversity. Further, a multicentre cohort study is required for application of results to the general population. Second, follow-up bias is inevitable in this prospective cohort study due to the existence of subjects who may migrate, leave or withdraw from this cohort, although the authors will try their best to control it.

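### The Discussion lets a significant association stand as evidence of a potential biomarker for predicting CVD events, but the stated analyses measure association only, and at this sample size significance can be reached at an AUC of about 0.55 to 0.58

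*Protocol article*

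**What the plan says.** The Discussion states in advance how a positive result will be read: "If the results of this study show a significant correlation between IgG glycosylated traits and actual clinical CVD composite events, it will provide". Two gains are then listed in the same sentence: support for the mechanism, and a potential biomarker for predicting CVD events in the clinic, described as better than GlycA. The condition is a significant correlation, and part of the conclusion is about prediction.

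The section Statistical and analytical plans names the tools: χ² tests, t-tests, analysis of variance and non-parametric tests for univariate comparisons, then logistic regression for the association of glycan characteristics with CVD events. After that "a glycan risk score will be created to evaluate the associative effects of all glycan traits screened". The stated criterion is p<0.05.

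The Abstract and Objectives describe the aim as correlation of glycan traits with events and plaque phenotypes, and the Introduction hypothesises an independent prognostic indicator. The Abstract also speaks of screening potential biomarkers. The one AUC in the article is in the Discussion, where a cited study is described as "displaying an area under the curve of approximately 0.7 in a cross-sectional study of Chinese Han"; that study separated people with dyslipidaemia from healthy people.

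**The concern.** A p value answers whether an association differs from zero. It depends on the number of events as well as on the strength of the association, so with enough events a weak association becomes significant. Prediction asks something else: how well the marker separates people who will have an event from those who will not, whether the predicted risks are right, and whether the marker adds to what is already known about the person.

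The Discussion moves from the first question to the second without a measure of the second. At stake is the reading of the primary-outcome result. A trait that barely separates future cases from non-cases could meet the article's stated condition and be reported as a potential predictive biomarker. Control of multiplicity or confounding would not cure this, because a well-controlled significant association is still only an association.

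**Working it through.** **Inputs, all from Sample size**
- Incidence of CVD events about 6%, with no time horizon given in the text.
- "2267 participants will be needed, based on an α of 0.05 on a two-sided test and 90% power".
- One-fifth added for losses: 2267 × 1.2 = 2720.4, given as 2720. This reproduces.

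**The plan's own 2267.** It equals 136/0.06 = 2266.7, that is, 136 events. It does not follow from the GP6 figures as printed, where the upper quartile of the comparison group (4.35) lies below its median (4.48). If that quartile is assumed to be 5.35 and the source groups are assumed to number about 80, the mean difference is 0.45 and the SDs are about 1.20 and 1.07. A 1:1 t-test then needs 136 per group, hence 2267. The check below uses only the sample size, the incidence and α, so it does not depend on this reconstruction.

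**Smallest observed effect that reaches two-sided p=0.05**, for one fixed trait, assuming normal values with equal SD:
1. Events = 0.06 × 2267 = 136; non-events = 2267 − 136 = 2131.
2. √(136 × 2131 / 2267) = 11.31.
3. Standardised difference d = 1.96 / 11.31 = 0.173.
4. Odds ratio per SD = exp(0.173) = 1.19.
5. AUC = Φ(d/√2) = Φ(0.1226) = 0.549. The rank-test form, 0.5 + 1.96 × √((N+1)/(12 × 136 × 2131)) with N = 2267, gives 0.550. In simulated logistic fits, those with p near 0.05 had a mean AUC of 0.550.
6. Share of events in the top 10% of trait values ≈ 1 − Φ(1.2816 − 0.173) = 0.134, so about 13% against 10% by chance.

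**True effect detected with 90% power** when 136 events are compared with 2131 non-events: d = (1.960 + 1.282)/11.31 = 0.287, odds ratio 1.33, AUC 0.580.

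**Sensitivity to incidence** (lower incidences are assumptions; same formulas, 2267 participants):

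| Incidence | Events | d at p=0.05 | Odds ratio per SD | AUC at p=0.05 |
|---|---|---|---|---|
| 6% | 136 | 0.173 | 1.19 | 0.549 |
| 4% | 91 | 0.210 | 1.23 | 0.559 |
| 3% | 68 | 0.241 | 1.27 | 0.568 |
| 2% | 45 | 0.295 | 1.34 | 0.583 |
| 1% | 23 | 0.411 | 1.51 | 0.614 |

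With all 2720 evaluable at 6% (163 events), the threshold AUC is 0.545. With an assumed Bonferroni correction for the 24 glycan peaks at 6% and 2267 participants, it is 0.576 (0.579 in the rank form).

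**What these figures do not cover.** They apply to a trait fixed in advance. The glycan score is to be built from traits screened in the same data, so its apparent AUC would tend to be too high. That is a reason to correct for optimism when the score is assessed.

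**The case against.** The case on the other side has real weight.

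- **The sentence is hedged and is not a decision rule.** It says potential, it is Discussion text, and no endpoint or stopping rule depends on it. The formal aims concern association, and the planned analyses suit them. This stands. A reader might infer that the protocol formally declares glycans a predictor on p<0.05; it does not. The hedge still does not supply the missing step from significance to prediction.
- **Performance measures may be in a document not shown.** A condensed article may leave the C-statistic and calibration to a full protocol or analysis plan. This stands too: a reader might infer that the study will not measure discrimination, and the article cannot show that. The point rests on the inference that the article itself states, which no separate plan makes valid as worded.
- **The AUC of about 0.7 is no benchmark.** A reader might infer that the article adopts 0.7 as its yardstick and that the study would fall short of it. The figure comes from a cross-sectional comparison in dyslipidaemia, a different task from predicting incident events, and the article sets it as no target.
- **0.55 is a minimum.** It is the least effect that just reaches significance, for one trait, at 6% incidence, and any cohort of adequate size can yield significance at a small effect. This is correct, and it is why the range is given. It is not a forecast of what the study will find. The 0.287 SD is likewise not shown to be the planning effect: the reconstruction of 2267 implies 0.45/1.138 = 0.40 SD, an AUC of about 0.61.
- **GlycA.** A reader might infer from the data list, which does not name GlycA, that a comparison is impossible. A condensed list cannot settle that, and this point does not depend on it.

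**Conclusion.** The concern holds in a limited form. The article draws a prospective conclusion about predicting CVD events from a significant correlation, while the analyses it states measure association only. For one fixed trait and 2267 participants, two-sided p=0.05 corresponds to an AUC of about 0.55 at 6% incidence and about 0.57 to 0.58 at an assumed 3% to 2%. These figures rest on normal trait values with equal SD in both groups, the stated sample size as evaluable, and α of 0.05 without multiplicity adjustment. Significance by itself therefore does not show useful prediction.

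The association analysis, the sample size and the data collection are unaffected. What needs correcting is the step from a significant odds ratio to a statement about prediction, together with the measures that such a statement would need.

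**What to change.** 1. In Statistical and analytical plans, state that the glycan score will be assessed by its C-statistic with 95% CI, corrected for optimism (for example by a bootstrap that repeats the screening of traits), because the traits are screened in the same data.
2. In the same section, add the change in C-statistic, with its CI, when the score is added to the risk factors already listed under Data collection and management (such as smoking history, diabetes status, antihypertensive medication and lipids), and calibration of predicted against observed 3-year risk.
3. If a full protocol or analysis plan already contains these, a reference to it is enough.
4. In the Discussion, reword the sentence so that a significant odds ratio supports only a statement that glycan traits are associated with CVD events. Any statement about predicting events should rest on the gain in C-statistic and its CI.

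The cost is a little more analysis on data already planned for collection, and one reworded sentence. The downside for the authors is that the headline claim may become weaker.
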